# **Delegation of Clinical Trial Duties**

Responsibilities for the conduct and oversight for the trial are delegated to you as the Coordinating Principal Investigator. You may delegate trial related responsibilities to the listed Principal Investigator(s) and any trial-related personnel. All trial-related duties delegated by the Coordinating Principal Investigator or Principal Investigator(s) and trial-related personnel must only be delegated to those that are qualified by experience and training. Delegated responsibilities must be retained in the [UNSW Clinical Trial Delegation Log](https://research.unsw.edu.au/document/Clinical%20Trial%20Delegations%20Log.docx). The UNSW Sponsor's Delegate is to be notified of the following:

- Protocol deviation reports outlined in the UNSW Research Misconduct Procedure.
- Any serious breach of Good Clinical Practice, the clinical trial protocol, the clinical trial standard operating procedures, or the human ethics approval that is likely to affect to a significant degree the safety or rights of participants or the reliability and robustness of the data generated in the clinical trial.
- Significant safety issues that are likely to (or have the potential to) affect to a significant degree the safety or rights of participants or the reliability and robustness of the data generated in the clinical trial.
- Urgent safety measures implemented to remove or prevent a significant safety issue.
- Safety reports relating to the continuation, suspension, or discontinuation of the clinical trial for safety reasons.
- Non-compliance with the protocol, SOPs, GCP, and applicable regulatory requirement(s) significantly affects or can potentially affect human subject protection or reliability of trial results significantly.
- Participant complaints or concerns received concerning the conduct of the research.
- Significant modifications to the clinical trial are likely to affect a significant degree the safety or rights of participants or the reliability and robustness of the data generated in the clinical trial.
- Addition of participating trial sites, contractual arrangements at participating sites or modifications to legal agreements.
- The intention to conduct the trial in other countries.

# **Trial Objectives and Purpose**

**Aim 1:** To evaluate the *efficacy* of Doing What Matters in Times of Stress (DWM) – a low-intensity mental health intervention – for refugees displaced in Indonesia.

- The hypothesis to be tested is that DWM (DWM workbook + five weekly facilitator sessions) will decrease psychological distress compared to a waitlist control group.

**Aim 2:** To evaluate the *mechanisms* underlying Doing What Matters in Times of Stress (DWM) – a low-intensity mental health intervention – for refugees displaced in Indonesia.

- The hypothesis to be tested is that reductions in psychological distress during and after the provision of DWM will be mediated by improvements in key psychosocial processes (psychological flexibility, emotion regulation, intolerance of uncertainty, and social functioning).

**Primary endpoint:**

This study will implement a waitlist control Randomised Controlled Trial design, where participants will be randomly assigned to active treatment (DWM) or a waitlist control condition (WL) on a 2:1 ratio.

The main study parameter will be psychological distress, measured using the Kessler Psychological Distress Scale – 10-item version (K10; Kessler et al., 2002). A description of this measure can be found under “Measurement Instruments”. This measure is administered at pre-treatment (including as a screening measure), mid-treatment, immediately post-treatment, and 1 month after the completion of treatment.

**Secondary endpoints:**

The measurement instruments are described under ‘Measurement Instruments’.

1. Severity of posttraumatic stress symptoms (PCL-5, 6-item version)
2. Presence and severity of suicidal ideation (SIDAS)
3. Self-identified problems (PSYCHLOPS)
4. Wellbeing (WHO-5)
5. Psychological Flexibility (adapted CompACT & AAQ-II)
6. Repetitive Negative Thinking (PTQ-Short Form)
7. Intolerance of Uncertainty (abbreviated IOUS)
8. Social satisfaction and functioning (abbreviated WHOQoL-BREF items and SAS-SR-modified)
9. Physical health (abbreviated WHOQoL-BREF)
10. Post-Migration Living Difficulties (adapted PMLD Checklist)
11. Exposure to adverse life events (adapted HTQ)
12. Use of emotion regulation strategies (adapted RESS-EMA)
13. Momentary emotions
14. Functional impairment (WHODAS-12)

**Other study parameters/endpoints (if applicable):**

The measurement instruments are described under ‘Measurement Instruments’.

1. Demographic data
2. Treatment fidelity (checklists)
3. Other indicators on intervention delivery: dose, perceived benefit, quality
4. Treatment contamination check

# **Background Information**

Many studies have shown that refugees suffer elevated rates of mental health problems, including depression, anxiety, and posttraumatic stress disorder (Blackmore, 2020). Providing effective mental health interventions for refugees is thus a critical priority for global public health. However, meeting this priority is challenging, as 99% of the world's refugees reside in low- and middle-income countries (LMICs) where access to psychological treatment is extremely limited (UNHCR, 2022). In an attempt to meet this challenge, the World Health Organisation (WHO) recently developed a set of low-intensity scalable mental health interventions, including Doing What Matters in Times of Stress (DWM) (Bryant, 2023). These interventions are ideally suited to LMICs as they teach psychological skills via lay refugee facilitators and self-help methods (thus requiring few resources).

The DWM intervention was selected for this current project for two reasons:

First, due to practical and logistical considerations. Barriers to the delivery and uptake of mental health interventions for refugees in Indonesia include a lack of financial resources to pay for lengthy treatment programs, limited capacity of mental health specialists to deliver specialized services, language barriers between the refugee and host communities and limited ability of refugees to travel to and from physical appointments. To address these barriers, DWM is: inexpensive, remotely delivered, of short duration, and is simple to train to local providers so that it can be made available rapidly to large numbers of people. This is highly relevant to the study context (refugees displaced in Indonesia), where demand for mental health services exceeds the availability.

Second, due to clinical considerations. DWM teaches core cognitive and behavioural techniques that our previous longitudinal research with refugees in Indonesia found to be relevant to promoting mental health in this context (Nickerson et al., 2022; 2023; HC190494). Moreover, we found high rates of *multiple* psychological problems. Contrary to traditional mental health programs, which usually focus on single psychiatric disorders (such as posttraumatic stress disorder; PTSD), DWM is transdiagnostic (i.e., not disorder-specific) to target common mental health symptoms and general psychological distress.

The WHO has developed the DWM intervention (which is part of a suite of low-intensity, short, less expensive and trans-diagnostic programs) to reduce psychological distress and improve psychosocial functioning. It is based on the WHO treatment guidelines for conditions related to stress (WHO, 2013). DWM is a remotely delivered intervention. Participants receive an illustrated workbook (comprising 5 ‘lessons’) and audio files, as well as 5 weekly calls from a trained non-specialised facilitator. The DWM lessons comprise evidence-based techniques from Acceptance and Commitment Therapy: (a) ‘Grounding’ (mindfulness skills), (b) ‘Unhooking’ (thought defusion techniques), (c) Acting on Your Values (values-guided behavioural activation and problem-solving), (d) Being Kind (consolidation of thought defusion techniques for unkind thoughts), (e) Making Room (consolidation of mindfulness techniques for emotional pain; self-care/self-compassion). An earlier derivative of DWM (Self-Help Plus – the face-to-face group version of DWM) was found to be effective for South Sudanese refugees in Uganda (Tol et al., 2020). Specifically, this trial found that the intervention resulted in significant reductions (at post-intervention and/or 3-month's follow-up) in psychological distress, PTSD, depression, functional impairment, subjective wellbeing and self-identified problems. Further, a secondary analysis found preliminary indications that psychological flexibility may be a mechanism of change driving intervention response (Lakin et al., 2023).

However, two gaps in our evidence-base remain. First, this earlier trial was conducted solely with women, in a face-to-face group-based format. To enhance the reach of the program to more people, this intervention has since been adapted for remote and individual delivery, where participants receive a workbook and audio files alongside calls from a trained facilitator. A pilot trial has demonstrated the feasibility of this approach for displaced refugees in Turkey (Acarturk et al., 2022), however a fully-powered efficacy trial of DWM has yet to be conducted. Second, to date, there has been very little interrogation of how DWM works (Lakin et al., 2023; Bryant, 2023). Without clear evidence on the mechanisms responsible for good mental health among refugees, we cannot refine these interventions to more effectively support refugee communities. This project will directly address these gaps by providing a comprehensive investigation of:

(1) the efficacy of the remote, individually delivered format of DWM among male and female refugees displaced in Indonesia, and

(2) the mechanisms of change within the DWM intervention.

The design of the current RCT has been informed by previous studies (Tol et al., 2020; Acarturk et al., 2023) and gold-standards for intervention evaluation. Trials conducted with refugee communities using DWM or similar WHO interventions (including trials with female refugees in Uganda (N=694), terrorism survivors in Pakistan (N=370) and gender-based violence survivors in Kenya (N=520)) have resulted in no direct adverse events. Participants are screened prior to commencing the program so that those requiring more specialized interventions are referred to experienced local service providers based in Indonesia (e.g., UNHCR and Church World Service). The DWM intervention is based on teaching coping skills and is not expected to provoke adverse reactions. These risks are justified by the benefits of the research described above.

**Population:**

Participants will be adult refugees (predominantly from Afghanistan and Iran) currently residing in Indonesia. This sample was selected for two key reasons. First, it represents the majority demographic of refugees displaced in Indonesia. It is estimated that Indonesia hosts approximately 12,000 displaced refugees, with over 50% originating from Afghanistan or Iran. Second, in a previous 2-year longitudinal study of the mental health and experiences of refugees in Indonesia, refugees from these countries of origin evidenced particularly elevated levels of psychological distress (symptoms of PTSD and depression; Nickerson et al., 2023).

# **Statement of Compliance**

The clinical trial will be conducted in compliance with the following guidelines and documentation:

- [ICH Guidelines for Good Clinical Practice (GCP)](https://www.tga.gov.au/publication/note-guidance-good-clinical-practice)
- [National Statement on Ethical Conduct in Human Research](https://nhmrc.gov.au/about-us/publications/national-statement-ethical-conduct-human-research-2007-updated-2018) (National Statement)
- As approved by the Human Research Ethics Committee (HREC), the clinical trial protocol is responsible for monitoring the trial's conduct.
- The responsibilities set out by the UNSW Sponsors Delegate.

The onsite or remote monitoring standard operating procedures as put in place by the clinical trial sponsor.

# **Trial Design**

A single-blind waitlist control RCT design will be used to answer the research questions (see ‘Schematic of Trial Design’ figure below). Participants will be randomized to either an active treatment (DWM) or waitlist (WL) control condition. For those in the active treatment condition, the intervention, DWM, will be delivered over a 5-week period. Participants will receive a workbook and audio files. The DWM workbook comprises 5 'lessons' that participants can work through in a self-paced format. Participants will receive 5-weekly calls by a trained facilitator, who will assist the participant in learning and practicing the key coping strategies of the program. Participants in the WL control condition will gain access to the DWM workbook and audio files following the completion of the WL period.

The trial is a single-blind randomised controlled trial, which means the outcome assessors are blind to treatment allocation. Randomization will be carried out by an independent researcher not involved in intervention delivery, clinical supervision, independent assessment or other aspects of the day-to-day running of the study. Randomization will be performed using computerized software on a 2:1 basis, such that double the number of participants are allocated to the active treatment condition. This randomization ratio was selected to ensure adequate power for study aim 2, to investigate the mechanisms of change *within* the active treatment.

**Schematic of Trial Design**

[figure not shown]

# **Sample Size**

We plan to enrol 303 participants into the trial. As a key focus of this study is to investigate psychological and social mechanisms underlying the impact of DWM on mental health outcomes, we will implement a 2:1 allocation ratio (DWM to WLC) to ensure analyses are adequately powered. Based on previous research, we aim to detect a medium between-groups effect size (0.40) (Tol et al., 2020; Acarturk et al., 2020) on our main outcome measure (Kessler-10). With alpha of 0.05 and power of 80%, we will need to include a minimum of 224 participants across both arms (150 in the DWM arm and 73 in the WLC). We estimate 35% attrition given the mobile nature of the refugee population in Indonesia, and thus we will need to recruit 303 participants into the trial.

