Participants deemed eligible based on the online screener and phone screener process will be invited to participate in the trial and sent a link to review the trial’s Participant Information Statement and Consent Form. Following informed consent, participants will be contacted to book their first assessment (Structured Assessment 1). Structured Assessments will be conducted by trained research assistants called ‘Assessors’ (see ‘Trial Personnel’ below) and will involve the administration of the scales in a structured interview format to assess mental health and psychosocial functioning (see ‘Measurement Instruments’ below). If, at the time of the baseline assessment (Structured Assessment 1), the participant’s symptoms of psychological distress have spontaneously improved such that they no longer score above the cut-off, they will be provided feedback on their test outcomes and it will be explained why they are no longer eligible for the study.

After the baseline assessment, participants will be randomized on a 2:1 (active treatment : waitlist control) basis by an independent research assistant, not involved in the assessments, using computerized software. Participants will be randomised to either the Active Treatment condition (*n*=214) or the Waitlist Control condition (*n*=107) to form a single-blind waitlist control RCT design. Participants in the Active Treatment condition will receive the 5-week DWM intervention from Weeks 1-5. Regardless of condition, all participants will complete Structured Assessments every 3 weeks.Upon completion of the final Structured Assessment (1-month follow-up, conducted 9-weeks following baseline assessment), participants in the Waitlist Control condition will gain access to the DWM workbook and audio files.

The instruments administered in Structured Assessments 2-4 closely resemble those used in Structured Assessment 1, with minor changes (as some scales do not need to be re-administered). This is outlined in the ‘Measurement Instruments’ section below. In case participants do not attend a scheduled assessment, the research team will attempt to contact them via follow-up text messages and/or phone calls for a maximum of eight times for scheduling a new appointment.

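### The 303 enrolment target adds 35% to 224 instead of allowing for 35% loss (which needs 345), and another section randomises 321

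*Protocol*

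**What the plan says.** The Sample Size section of the protocol gives a short derivation:

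- Effect: "we aim to detect a medium between-groups effect size (0.40"), on the K10.
- Allocation: "we will implement a 2:1 allocation ratio (DWM to WLC").
- Error rates and requirement: "With alpha of 0.05 and power of 80%, we will need to include a minimum of 224 participants across both arms", split as 150 in the DWM arm and 73 in the waitlist arm.
- Attrition and target: "We estimate 35% attrition given the mobile nature of the refugee population in Indonesia, and thus we will need to recruit 303 participants".

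Under Treatment of Subjects, the Trial Intervention text describes randomisation after consent and the baseline assessment: "Participants will be randomised to either the Active Treatment condition (*n*=214) or the Waitlist Control condition (*n*=107"). No total is given there, but the arms sum to 321. The section on withdrawal says that participants who withdraw are not replaced.

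**The concern.** There are two separate problems, and a small third one.

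1. **The attrition step.** The protocol presents 303 as the consequence of needing 224 and losing 35%. Adding 35% to 224 does not compensate for losing 35% of a larger number. If attrition is as forecast, the trial ends below its own stated minimum, and the 80% power claim is not supported by the calculation offered for it.
2. **Two trial sizes.** The protocol enrols 303 in one section and randomises 321 in another. Randomisation follows enrolment, so the randomised number cannot be the larger of the two. With both figures on record, a stop at 303, at 321 or in between could be described as according to plan.
3. **Arm minimums.** 150 and 73 sum to 223, not 224. This is one participant and matters only as a correction to make at the same time.

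**Working it through.** **Inputs**, all from the Sample Size section unless noted: standardised effect d = 0.40, alpha 0.05, power 80%, allocation 2:1, required number 224, attrition 35%, enrolment 303. From the Trial Intervention text: 214 and 107. The protocol does not say whether the test is one- or two-sided. Two-sided is assumed because only that reproduces 224.

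**Step 1: reproduce 224.** For 2:1 allocation with n in the smaller arm, the normal approximation is

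n = (z₀.₉₇₅ + z₀.₈₀)² × (1 + 1/2) / d² = (1.960 + 0.842)² × 1.5 / 0.16 ≈ 73.6, so 74, and 3 × 74 = 222 in total.

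With the t distribution, 150 + 75 = 225 is the first exact 2:1 split above 80%, and 150 + 74 gives 80.1%. So 224 is sound. A one-sided test would need 174, and 1:1 allocation 198, so neither is its source. The printed arms, 150 + 73 = 223, give 79.7%.

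**Step 2: the attrition step.**

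- As printed: 224 × (1 + 0.35) = 302.4, rounded up to 303.
- Needed to keep 224 after 35% loss: 224 / (1 − 0.35) = 344.6, rounded up to 345 (230 + 115).
- Attrition that 303 can absorb: 1 − 224/303 = 26.1%.
- Attrition that 321 can absorb: 1 − 224/321 = 30.2%.

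**Step 3: what remains at 35% loss.** Power is for the two-sample t test, two-sided 0.05, d = 0.40, with loss spread evenly over the arms:

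| Enrolled | Completers | Split (about) | Power | d detectable at 80% power |
|---|---|---|---|---|
| 303 | 303 × 0.65 = 197 | 131 : 66 | 75.0% | 0.426 |
| 321 | 321 × 0.65 = 209 | 139 : 70 | 77.4% | 0.413 |
| 345 | 345 × 0.65 = 224 | 149.5 : 74.75 | 80.3% | 0.399 |

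The normal approximation gives 75.4% and 77.7% for the first two rows. At 303 the trial finishes 224 − 197 = 27 short of its own minimum.

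**Step 4: effect of the planned baseline adjustment.** The Statistics section adjusts for baseline K10. If the correlation between baseline and outcome is r, the effective standardised effect is d / √(1 − r²). The protocol gives no r, so a range is shown at 35% loss:

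| r | Power at 303 | Power at 321 |
|---|---|---|
| 0 | 75.0% | 77.4% |
| 0.3 | 78.8% | 81.1% |
| 0.4 | 81.9% | 84.1% |
| 0.5 | 86.0% | 87.9% |

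The 80% mark is reached at r ≈ 0.34 for 303 and r ≈ 0.25 for 321.

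**The case against.** The strongest reply is that the shortfall is computed for an analysis that the trial will not run. The primary analysis is an intention-to-treat linear mixed model on all four structured assessments, with baseline K10 as covariate and missing data treated as missing at random. Someone who leaves before the 1-month follow-up still contributes earlier assessments, so treating all 35% as lost entirely is a worst case. Baseline adjustment alone would restore 80% at quite ordinary correlations. Even without it, the loss is about 5 percentage points at 303 and under 3 at 321, which does not threaten the validity of the primary result.

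All of this stands as a limit on the consequence. It does not rescue the derivation. The Sample Size section uses no baseline correlation and no gain from partial data. It says that 303 follows from 224 and 35%, and it does not.

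On the second number, one could say that the Sample Size section governs and the Trial Intervention text is only procedural. That tells a reader which figure to prefer but leaves the contradiction in place. It is tempting to explain 321 as 224 with 30% attrition, since 321 × 0.70 = 224.7. The protocol gives no such rate, so this is conjecture and nothing here depends on it.

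**Conclusion.** The concern holds. The required 224 is correct, but the step to 303 is an arithmetic error: 35% attrition calls for 345 on the protocol's own basis. Neither 303 nor 321 leaves 224 at that attrition. Power for an effect of 0.40 is about 75% at 303 and 77% at 321, against the stated 80%.

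These power figures assume a two-sided test, an unadjusted two-group comparison and even loss across arms. The planned baseline-adjusted mixed model may well reach 80% with either number, but that depends on a correlation that the protocol does not state. The conflict between 303 and 321 depends on none of these assumptions, and no reading of the text reconciles the two.

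**What to change.** Put one enrolment number, with its arm sizes, in both the Sample Size section and the Trial Intervention text. Which number is the sponsor's choice. The options are:

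- **Keep 303 (202 : 101)** and state about 197 completers at 35% attrition, about 75% power for 0.40 unadjusted, and a detectable effect of about 0.43.
- **Keep 321 (214 : 107)** and state about 209 completers, about 77% power and a detectable effect of about 0.41.
- **Keep 303 or 321 and re-base the power** on the planned baseline-adjusted analysis, giving the assumed baseline-outcome correlation and its source. About 0.34 is needed for 80% at 303, and about 0.25 at 321.
- **Enrol 345 (230 : 115)** if the stated effect, power and attrition are all to be kept on the present unadjusted basis.

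In every case, state that the test is two-sided, and correct the arm minimums to 150 and 74 (80.1% power) or 149 and 75 (80.3%), so that they sum to 224.

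The first three options change wording only: the stated power becomes slightly less favourable or is tied to an explicit assumption. The fourth costs 42 more participants than 303, or 24 more than 321.
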